**Primary outcomes**									
	Family Role Performance Scale	✔		✔		✔			
	Family Assessment Device-General Functioning Scale	✔		✔		✔			
**Secondary outcomes**									
	Care Management Strategies Scale	✔		✔		✔			
	Family Caregiver Conflict Scale	✔		✔		✔			
	Cantonese short version of Zarit Burden Interview	✔		✔		✔			
	The Patient Health Questionnaire-9 item	✔		✔		✔			
	Caregiving Ambivalence Scale	✔		✔		✔			
	Social care services used by stroke survivors	✔		✔		✔			
	Medical care services used by stroke survivors	✔		✔		✔			
	Clinical profile and service use data of stroke survivors							✔	
	Cost of study participation							✔	

#### Family Role Performance Scale

The research team developed this scale to measure the frequency and ability of the family member to perform 6 major family roles, that is, advisor, emotional connector, breadwinner, caretaker, decision maker, and caregiver by using the structure developed and validated by Chen et al [19]. This scale contains 2 parts. The first part contains 6 items and asks participants how often they perform the 6 family roles. Each item is answered on a scale ranging from 0 (*never*) to 4 (*very frequently*). The second part contains 6 items and asks participants to rate their performance regarding family roles. Each item is answered on a scale ranging from 0 (*very poor*) to 4 (*very good*). The 2 parts will be scored separately.

#### Care Management Strategies Scale

The research team developed this scale to measure caregivers’ care management strategies. The Care Management Strategies Scale consists of 18 items describing care management behaviors, including both positive and negative aspects, developed by the research team. The positive part contains 9 items and asks participants how often they perform positive care management strategies. Each item is answered on a scale ranging from 0 (*never*) to 4 (*very frequently*). The negative part contains 9 items and asks participants how often they perform negative care management strategies. Each item is answered on a scale ranging from 0 (*never*) to 4 (*very frequently*). The 2 parts will be scored separately, and then reverse coding will be applied to the negative part to provide a composite score. A higher score indicates better management strategies.

#### FCCS

The FCCS consists of 15 items to assess family conflict due to stroke. Each item is answered on a scale ranging from 1 (*strongly disagree*) to 5 (*strongly agree*). It has 4 subscales, namely, communication, problem-solving, general family functioning, and perceived criticism [16].

#### FAD-GF Scale

The FAD-GF scale is the 12-item general functioning of the McMaster Family Assessment Device [21] to measure the family functioning of caregivers. Each item is answered on a scale ranging from 1 (*strongly agree*) to 4 (*strongly disagree*).

#### Secondary Outcome Measures

The secondary outcome is related mainly to the personal level. Personal-level outcome measures include the Cantonese Short Version of Zarit Burden Interview (CZBI-short), Patient Health Questionnaire-9 item (PHQ-9), and Caregiving Ambivalence Scale. The study team will also obtain service utilization records and perform a cost-effectiveness evaluation. The details of each secondary outcome measure are described above (Table 3).

#### CZBI-Short

The CZBI-short is a spoken Cantonese version of the 12-item ZBI to assess the burden on Chinese dementia caregivers in clinical and social care settings [22]. Each item is answered on a scale ranging from 0 (*never*) to 4 (*very frequently*).

#### PHQ-9

The PHQ-9 is a reliable and valid instrument for assessing depressive symptoms in the general Hong Kong population. It consists of 9 items and was developed to correspond to the Diagnostic and Statistical Manual of Mental Disorders (Fourth Edition) criteria for major depression [23]. Each item is answered on a scale ranging from 0 (*not at all*) to 4 (*nearly every day*).

#### Caregiving Ambivalence Scale

The Caregiving Ambivalence Scale is adapted from the Intergenerational Ambivalence Scale [24] to measure the level of ambivalence between caregivers and care recipients. The scale for caregivers consists of 6 items—3 asking the positive components and 3 asking the negative components of their relationships. Each item is answered on a scale ranging from 0 (*never*) to 4 (*very frequently*).

#### Service Utilization Record

The service utilization of medical and social care services by stroke survivors was obtained. Medical care services include inpatient hospital admission, specialist outpatient, accident and emergency service, and hospital rehabilitation service. Social care services include home care service, daycare service, community rehabilitation service, and residential care service (admission after study intake). The clinical profile and service use data of stroke survivors and the electronic medical records from the Hospital Authority Clinical Management System of Hong Kong will be retrieved regularly until 6 months after the completion of the second follow-up assessment.

#### Cost and Cost-effectiveness Evaluation

In this study, the cost of study participation, including staff cost, travel expenses, and program materials, will be calculated. The research team will use the incremental cost-effectiveness ratio as well as the additional cost incurred to bring about one additional unit of a positive outcome to evaluate cost-effectiveness.

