### Objectives and Hypothesis

The main objective of this 8-12-week randomized controlled trial is to investigate the effectiveness and cost-effectiveness of a two-tier family-oriented intervention in enhancing the family functioning of caregivers of stroke survivors. We hypothesized that a two-tier family-oriented intervention for caregivers of stroke survivors can enhance their family functioning and care capacity as compared to a volunteer-led control intervention.

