### Sample Size Calculation

We used the G*Power 3 software (Psychonomic Society, Inc) to determine the minimum sample size required for obtaining a significant medium effect size of family functioning, given α=.05 and statistical power of 0.80, with a two-sided significance of .05. While we estimated the sample size, we could only take references from similar relevant studies reported in the literature that were available. References were taken from studies using individual-based outcomes such as the readmission rate of stroke survivors [17], depressive symptoms of caregivers [18], family role performance [19], and caregiver burden [4]. We admit that this is a limitation of our study. Based on a previous study, readmission rates within 6 months after discharge were significantly lower among patients who received follow-up home visits (26%-34%) compared to those who received standard aftercare only (44%) [17]. Besides, stroke accounts for 30%-50% of admissions to long-term residential care homes in Hong Kong [6]. To the best of our knowledge, since no intervention has utilized both care managers and volunteers in providing support to stroke families, we hypothesize that our designed intervention will lower the readmission rates of stroke survivors. As per this, we hypothesized that 15% of the stroke survivors whose caregivers were in the intervention group will be readmitted to a hospital or admitted to a residential care facility within 6 months after discharge, whereas 30% of the stroke survivors whose caregivers were in the control group will be readmitted to a hospital or admitted to a residential care facility over the same period. The resulting sample size estimate was 140 dyads per group; however, to ensure a sufficient effect size, and considering attrition, a sample size of 150 dyads per group will be used. We estimated that the attrition rate will be 25% based on the risk of second stroke occurrence within 1 year [20] as well as the fact that the previous intervention study lasted for around 6 months [17].

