### Statistical Analysis

We will use descriptive statistics to present baseline characteristics and outcome measures, and we will transform any skewed variables and correct their skewness before inferential analysis. To assess normality, we will perform the Shapiro-Wilk test of normality as well as the normal Q-Q Plot, while we will use the Wilcoxon signed-rank test for the nonparametric test. We will also perform the chi-square or independent two-tailed *t* tests to examine the differences in the baseline characteristics between the intervention and control groups. For the primary and secondary outcomes, we will perform a multi-factor analysis of variance or general linear model to compare the differential changes in each outcome across the 3 assessment time points, that is, T0, T1, and T2 between the 2 treatment groups. This model can account for repeated measures data that are intercorrelated and that produce unbiased estimates even in the presence of the missing data, provided that the data are missing at random. Multivariate regression will be used to compare the differences in the outcomes between the 2 treatment groups and will control for the effect of potential covariates such as depressive symptoms and caregiver burden. Recruitment rate, attrition rate, and missing data will also be examined and reported. All outcome measures will be analyzed based on intention-to-treat principles. Every participant who is randomized according to the randomized treatment assignment will be included. This method of analysis preserves the prognostic balance afforded by randomization [25]. The cost of study participation, including staff cost, travel expenses, and program materials, will be expressed in Hong Kong dollars. All the statistical analyses will be performed using SPSS Statistics. All statistical tests will be two-sided with the level of significance set at .05.

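### The cost-effectiveness evaluation names only programme delivery cost, so its ratio cannot show net cost to health and social care, although the trial records service use and expects admissions to fall

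*Protocol article*

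**What the plan says.** Cost-effectiveness is part of the main objective: the trial is to "investigate the effectiveness and cost-effectiveness of a two-tier family-oriented intervention in enhancing the family functioning of caregivers of stroke survivors" (Objectives and Hypothesis). The Abstract lists the incremental cost-effectiveness ratio among the secondary outcomes.

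The cost is described the same way in three places:
- Cost and Cost-effectiveness Evaluation: "the cost of study participation, including staff cost, travel expenses, and program materials, will be calculated".
- Statistical Analysis: "The cost of study participation, including staff cost, travel expenses, and program materials, will be expressed in Hong Kong dollars".
- Table 3: the only cost row is the cost of taking part in the study.

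The ratio is to be supplemented by the "additional cost incurred to bring about one additional unit of a positive outcome". That outcome is not named.

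Service use is described separately. "The service utilization of medical and social care services by stroke survivors was obtained" (Service Utilization Record), and "Medical care services include inpatient hospital admission, specialist outpatient, accident and emergency service, and hospital rehabilitation service". The social side covers home care, daycare, community rehabilitation and residential care. Hospital records are to be retrieved until 6 months after the second follow-up. The Sample Size Calculation adds that "we hypothesize that our designed intervention will lower the readmission rates of stroke survivors", with 15% against 30% having a hospital readmission or residential admission within 6 months of discharge.

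**The concern.** The trial collects the main items of health and social care cost and expects some of them to fall, but the cost named for the evaluation contains none of them. The intervention arm receives 6-10 home sessions, with care managers delivering the first tier. The control arm receives 4 volunteer visits and 2 telephone contacts, with no direct care-manager input. Delivery cost will therefore almost certainly be higher in the intervention arm. If nothing else is counted, any saving or extra spending on services does not reach the ratio. That matters for a trial whose Background cites the financial burden of poor recovery on the health system, and whose Discussion offers evidence on monetary value to the Hospital Authority and the Social Welfare Department.

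Two related choices compound this. The unit of effect is open. The stated analysis for all secondary outcomes, an ANOVA or general linear model over three time points, does not fit outcomes that Table 3 ticks only once.

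**Working it through.** The article gives no unit cost, incremental cost, ratio or threshold, so there is no cost figure to reproduce. What can be checked is the scope of the costs and what the protocol's own rates imply.

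**Cost scope.** Set side by side, the three statements of cost list staff, travel and materials, or simply the cost of participation. The word *including* introduces components of participation cost, and a survivor's hospital or residential admission is not a cost of participating. The Secondary Outcome Measures section mentions obtaining service records and performing the economic evaluation in one sentence, but as two tasks. It does not say that one feeds the other.

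**Break-even on the protocol's rates.** Inputs, from Sample Size Calculation: p_C = 0.30 and p_I = 0.15. Let D be the incremental programme cost per dyad and c the cost per event. Assume one costed event per affected survivor and no other difference in service use.

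- Net increment = D + c × (p_I − p_C) = D − 0.15c.
- It is zero when c = D / 0.15 = 6.67 D.
- In multiples of D: c = 0 gives 1.00 D; c = 2D gives 1 − 0.30 = 0.70 D; c = 6D gives 1 − 0.90 = 0.10 D; c = 12D gives 1 − 1.80 = −0.80 D.

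The same section cites readmission of 26%-34% with home visits against 44% with standard aftercare, a difference of 0.10 to 0.18. At those differences the break-even would be 1/0.10 = 10 to 1/0.18 = 5.6 times D. These figures come from a different comparison and serve only as a range. If service use rose instead, the delivery-only figure would understate the increment.

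**Observation window.** The intervention lasts 2-3 months, the second follow-up comes 2 months later, and record retrieval ends 6 months after that: 2 + 2 + 6 = 10 to 3 + 2 + 6 = 11 months from the start. The end point therefore moves with the length of the intervention. Costs need one fixed window for both arms.

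**Effect unit.** The Primary Outcome Measures section lists four scales; the Abstract and Table 3 list two. One of the two, the Family Role Performance Scale, has two parts scored separately. For the other, the FAD-GF, the article gives response anchors but no direction for improvement. Each choice yields a different ratio.

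**Analysis model.** Table 3 ticks the row "Clinical profile and service use data of stroke survivors" and the participation-cost row only at six months after the second follow-up. A model of change across baseline and two follow-ups cannot be fitted to a single tick. The planned transformation of skewed variables does not help the ratio either, because its numerator is a difference in arithmetic mean cost, which an analysis on a transformed scale does not estimate.

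**The case against.** The strongest reply is that this is a condensed article. No sentence excludes service costs, and perspective, unit costs and costing method are often left to a full protocol or analysis plan. That stands to this extent: the text is not a declaration that service costs are excluded. But the article does more than stay silent. It fixes a cost scope, repeats it, and nowhere connects the recorded services to it.

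A reader might infer that the evaluation cannot answer its objective. The documents do not support that. The objective concerns cost-effectiveness in enhancing family functioning and states no perspective. Added programme cost per unit of family functioning answers it from the provider's side.

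A reader might also infer that all service use is collected once, after the second follow-up. That is wrong: Table 3 has separate rows for medical and social services used, both ticked at baseline and both follow-ups. Only the record-data and participation-cost rows have a single tick, and even the records are said to be retrieved regularly.

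Two further points stand. A higher delivery cost in the intervention arm is real, not a bias, and control volunteers are also supervised by care managers. The 15-point difference is a proportion of survivors with a composite event, not a count of admissions. Repeat admissions and the continuing cost of residential care are not captured by it, and its 6 months run from discharge, not from randomisation.

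**Conclusion.** The point holds in limited form. As written, the evaluation yields a delivery-cost ratio: a narrow provider view that cannot show net cost to the health and social care system, towards which the rationale and policy aim are directed. The amount left out cannot be fixed from the article, and any figure in Hong Kong dollars would rest on outside prices. What the protocol's rates do give is a threshold: the increment changes sign if the cost per event exceeds about 6.7 times the incremental programme cost. This assumes that the hypothesised 30% to 15% fall occurs, that each affected survivor has one costed event, and that other service use does not differ. The omission could therefore change the economic conclusion, but whether it does is unknown. The effect unit and the model for the record-based data are smaller defects of the same evaluation. None of this touches the primary comparison of family functioning.

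**What to change.** - State the costing perspective. Add a ratio whose incremental cost is programme cost plus unit cost times each recorded medical and social service, over one common window from randomisation that record retrieval covers in both arms.
- Base it on untransformed arithmetic mean costs, with bootstrap intervals for incremental cost and effect.
- Name one primary scale (and one part, if the scale has two) as the effect unit, with improvement coded positive.
- Report the programme-cost-only ratio alongside, labelled as the provider view.
- For the record-based admission data, replace the three-time-point ANOVA or general linear model with a between-group model, for example logistic regression for any readmission or residential admission within the window.

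The service data are already part of the plan, so the added work is a unit-cost list and the analysis. The price is wider intervals, because service costs are skewed.

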### Statistical Analysis

We will use descriptive statistics to present baseline characteristics and outcome measures, and we will transform any skewed variables and correct their skewness before inferential analysis. To assess normality, we will perform the Shapiro-Wilk test of normality as well as the normal Q-Q Plot, while we will use the Wilcoxon signed-rank test for the nonparametric test. We will also perform the chi-square or independent two-tailed *t* tests to examine the differences in the baseline characteristics between the intervention and control groups. For the primary and secondary outcomes, we will perform a multi-factor analysis of variance or general linear model to compare the differential changes in each outcome across the 3 assessment time points, that is, T0, T1, and T2 between the 2 treatment groups. This model can account for repeated measures data that are intercorrelated and that produce unbiased estimates even in the presence of the missing data, provided that the data are missing at random. Multivariate regression will be used to compare the differences in the outcomes between the 2 treatment groups and will control for the effect of potential covariates such as depressive symptoms and caregiver burden. Recruitment rate, attrition rate, and missing data will also be examined and reported. All outcome measures will be analyzed based on intention-to-treat principles. Every participant who is randomized according to the randomized treatment assignment will be included. This method of analysis preserves the prognostic balance afforded by randomization [25]. The cost of study participation, including staff cost, travel expenses, and program materials, will be expressed in Hong Kong dollars. All the statistical analyses will be performed using SPSS Statistics. All statistical tests will be two-sided with the level of significance set at .05.

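### The test of family functioning treats the baseline score as a third outcome instead of a covariate: it is valid, but gives up power that adjusting for the scale's own T0 value would recover

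*Protocol article*

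**What the plan says.** The hypothesis (Protocol article, Objectives and Hypothesis) is that the two-tier intervention "can enhance their family functioning and care capacity as compared to a volunteer-led control intervention". It has a direction but names no time point.

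For primary and secondary outcomes alike, the Statistical Analysis section offers a multi-factor ANOVA or, as an alternative, a general linear model. The stated aim is this: "compare the differential changes in each outcome across the 3 assessment time points, that is, T0, T1, and T2 between the 2 treatment groups". T0 is therefore one of the three compared occasions. No model term, contrast or degrees of freedom is named.

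The same section adds: "Multivariate regression will be used to compare the differences in the outcomes between the 2 treatment groups". The covariates it gives as examples are depressive symptoms and caregiver burden. The baseline value of the family-functioning scale is not among them, and no outcome time point is given. On error rates it says: "All statistical tests will be two-sided with the level of significance set at .05".

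The only effect size given for this outcome is in Sample Size Calculation, which refers to the "minimum sample size required for obtaining a significant medium effect size of family functioning". It attaches no number to medium.

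**The concern.** A between-arm difference in change over three occasions is most naturally the group-by-time interaction, which has 2 degrees of freedom for two arms and three times. That test estimates the arm difference at T0 as a free quantity and subtracts it in full from the differences at T1 and T2. In a randomized trial the T0 difference is chance alone. Subtracting it in full adds noise unless the correlation between baseline and follow-up is 1. Using T0 as a covariate subtracts only the part that the correlation supports.

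Two things are at stake. The first is power: a real benefit of modest size could be missed by this test and detected in the same data by an adjusted one. The second is interpretation: a significant interaction does not itself say in which direction, or at which follow-up, the arms differ, and the hypothesis is directional.

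**Working it through.** The protocol states no power for this test, so there is no figure to reproduce. Its 140 per group is tied to proportions readmitted or admitted to residential care, not to family functioning.

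**Inputs**
- Two-sided 0.05: Statistical Analysis.
- 100 per arm: Results reports 200 completed baseline questionnaires. An equal split and no later loss are assumed.
- Effect *d* in SD units: 0.3 assumed; 0.5 as the usual reading of medium, also an assumption.
- Equal correlation *r* among T0, T1 and T2: 0.5 assumed, varied below.

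**Matrices** (SD = 1)
- Planned test: covariance *V* of the changes T1−T0 and T2−T0 has diagonal 2(1−r) and off-diagonal 1−r.
- Adjusted test: covariance *R* of T1 and T2 given T0 has diagonal 1−r² and off-diagonal r−r².
- With *x* the vector of effects at T1 and T2, noncentrality is (n/2) x′V⁻¹x or (n/2) x′R⁻¹x. Power comes from the noncentral F on 2 df (denominator 197 planned, 196 adjusted).

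*V* equals *R* plus (1−r)² added to every entry. Check: 1−r² + (1−r)² = 2(1−r), and r−r² + (1−r)² = 1−r. So *V* is never smaller than *R*, and the adjusted noncentrality is never below the planned one, whatever the effect profile. The only price is one denominator df.

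**Sustained benefit.** Planned n d²/[3(1−r)] = 100 × 0.09/1.5 = 6.0. Adjusted n d²/[(1−r)(1+2r)] = 100 × 0.09/(0.5 × 2) = 9.0. The ratio is (1+2r)/3 = 0.667.

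**Effect halves by T2** (0.3, 0.15). Planned 50 × 1.333 × (0.09 + 0.0225 − 0.045) = 4.5. Adjusted 50 × [1.5 × 0.1125 − 0.045] = 6.19.

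**T1 only** (0.3, 0). Planned 50 × 1.333 × 0.09 = 6.0. Adjusted 50 × 1.5 × 0.09 = 6.75.

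| Profile (n = 100 per arm, 0.3 SD, r = 0.5) | Planned | Adjusted for T0 |
|---|---|---|
| Sustained | 58% | 76% |
| Halves by T2 | 45% | 59% |
| T1 only | 58% | 63% |

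A simulation of 20,000 trials per row agreed: 57.9% v 76.0%, 45.2% v 58.3%, 58.0% v 62.9%. With no effect, the rejection rates were 5.0% and 4.9%.

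**Sensitivity, sustained benefit** (noncentrality in brackets)

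| n per arm | d | r | Planned | Adjusted |
|---|---|---|---|---|
| 100 | 0.3 | 0.3 | 44% (4.29) | 71% (8.04) |
| 100 | 0.3 | 0.7 | 81% (10.0) | 89% (12.5) |
| 75 (25% attrition from 100) | 0.3 | 0.5 | 45% (4.5) | 63% (6.75) |
| 100 | 0.5 | 0.5 | 96% (16.7) | over 99% (25.0) |
| 100 | 0.5 | 0.3 | 88% (11.9) | 99% (22.3) |

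At 0.5 SD the gain is under 5 points at r = 0.5. It shrinks further as r or n rises, because the planned test is already at 96% or more.

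**One-df average of T1 and T2, adjusted for T0** (n = 100, r = 0.5). The residual variance of the mean is (0.75 + 0.25)/2 = 0.5. A sustained 0.3 gives 50 × 0.09/0.5 = 9.0 on 1 df, power 85%. A T1-only effect has mean 0.15, giving 50 × 0.0225/0.5 = 2.25, power 32% against 58% for the planned test.

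**The case against.** The strongest reply has four parts.

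- **The null is not wrong.** A reader might infer that testing for parallel profiles asks a different question from whether there is a benefit after the intervention. The documents do not support that. With expected T0 means equal by randomization, parallel profiles and no arm difference at T1 and T2 are the same null. Type I error is about 5% either way. This stands: the issue is efficiency, not validity.
- **The size depends on values the protocol does not give.** A reader might infer a loss of 20 to 28 points. That range needs an effect of about 0.25 to 0.30 SD, correlation near 0.5, 100 to 132 per arm, and comparison with a baseline-adjusted 1-df average. At 100 per arm and 0.3 SD that gap is 58% to 85%. About 10 points of it come from the extra degree of freedom (a 1-df change contrast has 68%) and the rest from baseline adjustment. At the protocol's medium effect, with correlation at least 0.5 and 100 or more per arm, the gap is 0 to 4 points. This stands too.
- **Averaging T1 and T2 is a trade-off.** The protocol does not say that the effect will persist to T2, and the average does much worse if it does not (32% v 58%). So the average cannot be recommended outright.
- **The test is inferred.** The text allows a general linear model and a further regression, and an analysis plan not shown may name terms and contrasts. This is fair, and the absence of those details is not the complaint. The complaint is that the stated comparison includes T0 as an outcome occasion. The stated regression illustrates its covariates without the scale's own baseline.

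None of these reaches the baseline-adjustment point, which holds for every effect profile.

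**Conclusion.** The planned comparison is a valid test but an inefficient one, because T0 enters as an outcome with full weight. Adjusting for the scale's own T0 value gains about 18 points of power for a sustained benefit, 14 for a fading one and 5 for a T1-only one, assuming 0.3 SD, equal correlation 0.5, complete data and 100 per arm. The gain is larger at lower correlation and smaller at higher. For a sustained medium effect with correlation of at least 0.5 it is under 5 points, so a reader should not infer that the trial is underpowered at its own stated effect size because of this choice. The conclusion rests on reading the comparison as group-by-time, which is the natural reading but is not spelled out. The change is worth making because it does not depend on guessing the shape of the effect.

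**What to change.** In Statistical Analysis, replace the comparison of changes over T0, T1 and T2 with a repeated-measures model in which T1 and T2 are the outcomes and the scale's own T0 value is a covariate. An equivalent choice keeps T0 in the model but constrains the two arms to a common T0 mean. Report the adjusted between-arm difference at T1 and at T2, each with a 95% CI and its direction, so that the hypothesis is answered directly.

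The constrained form has a practical advantage. Results reports 264 enrolled and 200 baseline questionnaires, so 64 have no T0 score. Any of them with follow-up data would drop out of a plain covariate model but stay in the constrained one, in keeping with the intention-to-treat commitment.

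A single average of T1 and T2 is an option only if a sustained benefit is expected and that expectation is stated in advance.

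The cost is wording and one denominator degree of freedom; no new data are needed. Because Results says that data collection and data set construction are complete, the change should be dated and documented before any comparison by arm. If that point has passed, report the group-by-time result beside the adjusted one.

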## Results

The clinical trial began recruiting in January 2017, and recruitment was completed at the end of April 2019. Data collection and data set construction were completed at the end of March 2020. As of March 2020, enrollment has been completed (n=264 stroke caregivers). A total of 200 participants completed the baseline questionnaires. We aim to publish the results by mid-2021. The intervention protocol is in Traditional Chinese only and is available upon request from the corresponding author.

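### The named primary model (multi-factor ANOVA or general linear model) does not have the missing-at-random validity claimed for it and does not fit the promise to include every randomised participant

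*Protocol article*

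**What the plan says.** All the relevant text is in the Statistical Analysis section of the protocol article, apart from two counts.

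- **Model:** "we will perform a multi-factor analysis of variance or general linear model to compare the differential changes in each outcome". This covers T0, T1 and T2, for primary and secondary outcomes alike.
- **Property claimed:** the next sentence says this model allows for correlated repeated measures and will "produce unbiased estimates even in the presence of the missing data, provided that the data are missing at random".
- **Analysis set:** "All outcome measures will be analyzed based on intention-to-treat principles". The section then adds that no one randomised is to be left out: "Every participant who is randomized according to the randomized treatment assignment will be included".
- **Software:** "All the statistical analyses will be performed using SPSS Statistics". No procedure is named.
- **Missing data:** "Recruitment rate, attrition rate, and missing data will also be examined and reported". The section names no mixed model, likelihood method or imputation.
- **Counts:** Sample Size Calculation expects 25% attrition. Results gives 264 caregivers enrolled and states: "A total of 200 participants completed the baseline questionnaires".

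**The concern.** Validity under missing at random (MAR) belongs to likelihood-based models fitted to all available scores, or to multiple imputation. It does not belong to analysis of variance or the general linear model as such. The section therefore gives one model three attributes that it does not jointly have: correlation within persons, validity under MAR, and inclusion of everyone randomised.

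An analyst who follows the text literally in SPSS could run GLM, which is a separate procedure from MIXED. The result would come from caregivers with complete data but would be reported as intention to treat and as unbiased under MAR. If caregivers leave after T1 for reasons related to their T1 score, and those reasons differ by arm, the comparison of change can show an effect that does not exist. Scores collected from incomplete cases would also be discarded.

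**Working it through.** The plan gives no figure for this point, so there is none to reproduce. The check has three parts.

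**1. The ways of running the named model**

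| Reading | Keeps incomplete cases? | Models within-person correlation? | Valid under MAR in general? |
|---|---|---|---|
| SPSS repeated-measures GLM | No, needs T0, T1 and T2 | Yes | No |
| Plain long-format ANOVA with time as a factor | Yes | No | No |
| ANOVA with participant as a factor | Yes | Yes, in a simple form | Not guaranteed |
| Likelihood-based mixed model (not named) | Yes | Yes | Yes, if correctly specified |

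Only the last row fits the claimed property, and the protocol does not name it.

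**2. How many a repeated-measures GLM would analyse**

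Inputs: 264 enrolled and 200 with baseline (Results); 25% attrition and 300 planned (Methods).

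- Without a baseline questionnaire: 264 − 200 = 64, and 64/264 = 24.2%.
- Planned maximum: 300 × 0.75 = 225.
- All 264 randomised, a single 25% loss: 264 × 0.75 = 198 (75%).
- All 264 randomised, 64 without T0, then 25% of the rest lost: 200 × 0.75 = 150, and 150/264 = 57%.
- The 64 never randomised: 150 of 200 (75%).

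**3. Size of the bias under MAR dropout**

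The documents give no correlations or dropout mechanism, so these are assumptions: 132 per arm (264/2), SD 1, true effect 0, 25% missing T2, and correlations T0–T1 0.6, T1–T2 0.7, T0–T2 0.4. Dropout after T1 depends on the T1 score with a log-odds slope of 1 per SD. There were 3,000 replicates, and ranges cover repeated runs.

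| Dropout depends on T1 | Complete-case T1 − T0 contrast | False positives at T1 | T2 − T0 contrast | False positives at T2 |
|---|---|---|---|---|
| In one arm only | 0.08–0.09 SD | about 10–11.5% | 0.02 SD | about 5% |
| In opposite directions by arm | 0.17 SD | 26–28% | 0.04 SD | about 6% |
| Equally in both arms | 0 | about 5% | 0 | about 5% |
| Not at all (MCAR) | 0 | nominal | 0 | nominal |

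Likelihood-based estimates from the same data were unbiased to within simulation error.

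A hand check agrees. If selection acts on T1 alone and shifts the completers' mean T1 by δ in an arm, mean change shifts by δ(1 − ρ01) at T1 and by δ(ρ12 − ρ01) at T2.

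- Opposite directions at T1: 0.17 = 2δ(1 − 0.6), so δ ≈ 0.21.
- One arm at T1: 0.21 × 0.4 ≈ 0.08.
- Opposite directions at T2: 2 × 0.21 × (0.7 − 0.6) ≈ 0.04.

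The T2 bias is therefore small because the two adjacent correlations were assumed to be similar.

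A second set used equal correlations across visits, a slope of 1.5 and opposite directions by arm (400 replicates). The T1 contrast at a true null was 0.41, 0.29 and 0.18 SD for correlations 0.3, 0.5 and 0.7. The mixed model gave 0.005, 0.002 and 0.004. The T2 contrast was unbiased.

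One qualification applies to equal dependence in both arms. It leaves no bias at a true null, but with a true effect of 0.5 SD in this second set the complete-case T1 contrast was 0.43, 0.45 and 0.47, so the effect was mildly understated.

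**The case against.** The strongest reply is that the authors meant a linear mixed model and mislabelled it. Their description of correlated measures, MAR and all randomised participants fits one, and the same software provides it. This is plausible, but then the model name is wrong and still has to be corrected.

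A reader might infer three stronger things that the documents do not support.

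- **That the plan deletes incomplete cases.** Nothing mentions listwise deletion, complete cases or an SPSS procedure. Deletion follows from the repeated-measures GLM reading only. A long-format or participant-factor ANOVA would keep incomplete cases, although neither earns the MAR claim.
- **That only 57% of those randomised would be analysed.** The 264 are described as enrolled, not randomised, and the flow diagram is not available in the text reviewed. The 24% shortfall at baseline may itself be part of the planned 25%, so applying 25% again may count the same loss twice. The figure is a lower end, not an expectation.
- **That the primary result will be biased.** The bias depends on assumed dropout that differs by arm. Sample Size Calculation bases its attrition on second stroke and study duration, not on T1 scores. The arms do differ in contact (6–10 sessions in one; four visits and two calls in the other), so differential dropout is possible, but it is not documented.

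It is also fair that covariance structure and imputation details belong in an analysis plan. Their absence here is not the point. The point is a property stated for a model that lacks it.

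**Conclusion.** The point stands as a wrong statement about the primary analysis, and no other section repairs it. On any ordinary reading, the named model does not have the claimed MAR validity, and as a repeated-measures GLM it cannot include every randomised participant.

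The size is conditional. With repeated-measures GLM and 25% attrition, about three quarters of caregivers would be analysed, and possibly as few as about 150. If dropout also depends on T1 differently by arm, the T1 contrast is off by roughly 0.08 to 0.17 SD, with 10% to 28% false positives, under correlations of 0.6, 0.7 and 0.4. It is off by up to about 0.4 SD with weaker correlations and steeper dropout. At T2 the bias is 0.02 to 0.04 SD with near-nominal error. It is nil under MCAR and, at a true null, under equal dependence in both arms. Correlations, SD and dropout mechanism are assumptions. That the claimed property does not hold for the named model does not depend on them.

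**What to change.** In Statistical Analysis, replace the named model with a likelihood-based linear mixed model for repeated measures (SPSS MIXED) that has arm, time and arm × time as fixed effects and models the within-person covariance. Fit it to all available scores from every randomised caregiver, including those who lack one or two of T0, T1 and T2. Attach the MAR sentence to this model only.

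A mixed model cannot recover caregivers with no outcome data at all. Report their number by arm, and state how many of the 264 enrolled were randomised and whether the 64 without a baseline questionnaire have T1 or T2 scores. Do not describe the analysis as including every randomised participant unless those without data are handled, for example in a multiple-imputation sensitivity analysis.

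If the investigators do intend repeated-measures GLM, the MAR sentence and the all-randomised claim should be withdrawn and the analysis described as complete-case. That is the weaker choice.

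The cost is a change of analysis wording. The procedure is in the software already specified, and no new data are needed.
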